### Pain medication management

PMM is an integral part of pain management in multidisciplinary clinics. In this trial, PMM consists of patient education about pain and pain medications, and advice on OM reduction. A *Pain and Medication Management Information Brochure* has been developed to standardise PMM across all centres. In the fifth week, MDs explains to participants the impact of chronic pain, and the potential problems associated with OMs. OM reduction schedules are developed and explained to each participant at the interview. The schedule is flexible and individually tailored. It includes instructions for which type of OM to reduce first, how much and when, the alternative medications and what to do if pain increases. In general, short-acting OMs are reduced first, then the long-acting (slow-release) OMs. Participants are asked to reduce their OM dosage by 30% in week 8, 50% by week 11 and 75% to 100% by Week 14. Participants are asked to reduce OM as long as their pain is not worse. If increased pain causes distress or dysfunction, participants can increase their OM dose to the previous level or take alternative non-opioid medications prescribed by MDs. Clonidine may be prescribed for participants experiencing opioid withdrawal symptoms as judged by the MDs. The dosages of all pain relief medications are recorded.

As part of PMM, during the 10-week treatment and the three-month follow-up periods, a trained researcher will make a phone call to all participants three times during the treatment and once a month during the follow-up period to remind participants of the OM reduction schedule. During the trial period, participants are instructed to continue their routine therapies.

### Therapists

EA is provided by registered acupuncturists with at least three years of clinical experience. PMM is given by MDs at the pain management centres. All therapists undergo pre-trial training regarding the trial procedures. An *Acupuncture Treatment Manual* has been developed for training acupuncturists; and the *Pain and Medication Management Information Brochure* is used for training MDs.

### Co-interventions

Co-interventions are discouraged. Participants using other therapies for CMP such as herbal medicine, physiotherapy, chiropractic and osteopathy are required to either discontinue them before entering into the trial or maintain their use during the trial and record use in their diaries.

### Withdrawal

Participants who find their pain significantly worse or cannot tolerate EA may terminate their involvement in the study. They are assessed by one of the MDs with advice on alternative management strategies for their condition. Their data will be treated as missing data.

### Assessment of efficacy

A list of outcome measurement tools and when they are administered are listed in Table 1.

**Table 1 T1:** Outcome measures to be administered throughout the trial

**Outcome measures**	**Components measured**	**Baseline**	**Treatment period**			**Follow-up period**		
		**W1**	**W5**	**W10**	**W14**	**W18**	**W22**	**W26**
**Questionnaires to assess outcomes of the treatment**								
Diary	Pain OM use non-OM use	✓ W1 to W4	✓	✓	✓	✓	✓	✓
Beck Depression Inventory	Mental status	✓	✓	✓	✓	✓	✓	✓
SF-36v2	Quality of life		✓	✓	✓	✓	✓	✓
Roland Morris Disability Questionnaire	Functionality		✓	✓	✓	✓	✓	✓
Short Opiate Withdrawal Scale	Withdrawal symptoms		✓	✓	✓	✓	✓	✓
Survey of patients’ attitude	Changes of attitudes		✓	✓	✓	✓	✓	✓
Chinese Medicine Chronic Pain Questionnaire	Pain and non-pain signs and symptoms	✓	✓	✓	✓			
**Questionnaires to assess credibility, expectancy and attitude to acupuncture or pain medications**								
Perception of EA treatment			✓(W6)		✓			
Acupuncture Expectancy Scale			✓(W5)					
Knowledge of Acupuncture		✓						
Pain Medication Questionnaire		✓						
**Elements of neuropathic pain**								
S-LANSS			✓(W5)					

OM: opioid medication; EA: electroacupuncture; SF-36v2: 36-item Short-Form Health Survey version 2; S-LANSS: self-report Leeds Assessment of Neuropathic Symptoms and Signs; W: week.

#### *Primary outcome measure*

The primary outcome measure is the change in OM between baseline and the end of the treatment period. OM usage is recorded daily in the Medication and Pain Diaries during the run-in period (between the first and fourth weeks), treatment period (between the 5^th^ and 14^th^ weeks) and follow-up period in the 18^th^, 22^nd^ and 26^th^ weeks. To make meaningful comparisons on medication use, the dosage of OM will be converted into morphine equivalent dose for data analysis [25].

#### *Secondary outcome measures*

Secondary outcome measures assess pain; impact of pain including function, quality of life and depression; consumption of non-opioid medications; and participants’ attitude to pain. All instruments have been widely used and demonstrated reliability and validity in the chronic pain population.

The outcome measures are as follows:

1. Number of participants who achieve 50% OM reduction at the end of the treatment and follow-up periods.

2. Type, severity and incidence of OM-related common AEs. Common AEs are somnolence, mental clouding, nausea and constipation. Uncommon AEs are fatigue, itching, adverse mood changes and dry mouth. They are assessed using visual analogues scale (0 = no symptom at all, 10 = very severe) to indicate the severity of these events.

3. Consumption of non-opioid medications.

4. Pain intensity measured with visual analogue scale (0 = no pain; 10 = worst pain possible) in the Medication and Pain Diary.

5. Quality of life assessed with 36-item Short-Form Health Survey version 2 (SF-36) [26].

6. Severity of depression assessed with the Beck Depression Inventory [27].

7. The level of function assessed with the Roland Morris Disabilities Questionnaire [28].

8. The presentation and severity of withdrawal symptoms assessed with Short Opiate Withdrawal Scale [29].

9. Participants’ attitude of pain assessed with Survey of Patients’ Attitude [30].

10. Chinese Medicine Chronic Pain Questionnaire, which we have developed to assess pain and non-pain signs and symptoms.

To make meaningful comparisons of non-opioid medications usage, the dosage of such medications is calculated according to Medication Quantification Scale Version III [31]. The Perception of EA Treatment Questionnaire [18] is given to the two acupuncture groups to assess the success of blinding in the 6^th^ and 14^th^ weeks. We also use Self-reported Leeds Assessment of Neuropathic Symptoms and Signs [32] to assess the certainty of neuropathic component of the pain.

### Assessment of safety and report of serious adverse events

An AE record form is attached to the end of the Medication and Pain Diaries so that participants can record any unexpected signs, symptoms and feelings during and after the treatment period. Acupuncture-related AEs are dizziness, fatigue, pain, bruising and infection. These will be scored using six-point scales (0 = none, 1 = minimal, 2 = mild, 3 = moderate, 4 = severe, and 5 = extremely severe). Participants are educated to differentiate AEs that are acupuncture-related from those that are OM-related. The former is usually short-lasting, whereas the latter persists when OM is consumed. Similarly, the acupuncturists will be required to record any adverse reactions during and after each treatment session. The likelihood that serious AEs reported by participants and acupuncturists are EA-related or OM-related will be assessed by two team members (ZZ, RH). They also consult, as appropriate, with the participant, MDs, and/or acupuncturists. The result of the assessment is recorded.

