### Aims

In this multicentre, randomised, sham-acupuncture controlled, three-arm clinical trial, we will evaluate the effect of EA as an adjunct therapy to PMM on OM consumption by patients with CMP. The primary hypothesis is that EA reduces OM consumption significantly more than sham EA. The secondary hypotheses are that:

1. the proportion of participants who experience 50% or more OM reduction is significantly higher in the EA group than that in the sham EA group;

2. EA reduces OM-related AEs significantly more than sham EA;

3. EA combined with PMM is significantly better than PMM alone in reducing OM usage and AEs;

4. EA reduces the intensity of pain and improves function significantly better than sham EA;

5. participants having a strong self-reliant attitude to pain consume significantly less OM than those relying on medications for pain relief.

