### Statistical analysis of the trial outcomes

The Statistical Program for Social Science (SPSS, the latest version) is used for data analyses. Baseline categorical data, demographic characteristics such as gender and age category, and numerical data are analysed with *χ*^2^ tests and one-way analysis of variance, respectively, to determine comparability of the three groups on these variables.

Linear mixed models (for continuous outcome variables) and generalised estimating equations (for categorical outcome variables) are used to examine the changes over time in weekly dosage of OM, numbers and types of OM-related AEs, severity of pain and Beck Depression Inventory. *χ*^2^ tests are also used to detect group differences in the numbers of dropouts and AEs.

Both intention-to-treat and per protocol analyses are used. Data from participants who do not violate the treatment protocols will be included in the per protocol analysis. Missing data are dealt with using the last value carried forward method. Missing Beck Depression Inventory and SF-36 data are dealt with according to the relevant manual.

Apart from the effects of types of intervention, the influence on the outcomes of differences between centres and therapists is also analysed. The relationship between OM reduction and attitude to pain are explored.

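### Comparisons of opioid-related AEs are open to attribution bias, most clearly EA versus no-EA, and the added chi-square on AE numbers ignores clustering if it counts events

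*Protocol article*

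**What the plan says.** Two secondary hypotheses in the Aims concern adverse events. Hypothesis 2 is that "EA reduces OM-related AEs significantly more than sham EA". Hypothesis 3 is that "EA combined with PMM is significantly better than PMM alone in reducing OM usage and AEs".

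Under Secondary outcome measures, item 2 is "Type, severity and incidence of OM-related common AEs". It then names two groups of symptoms: "Common AEs are somnolence, mental clouding, nausea and constipation", and "Uncommon AEs are fatigue, itching, adverse mood changes and dry mouth". Severity is rated on a 0-10 visual analogue scale.

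The safety section has a second list: "Acupuncture-related AEs are dizziness, fatigue, pain, bruising and infection". These are scored on a six-point scale, 0 to 5. On cause it says "Participants are educated to differentiate AEs that are acupuncture-related from those that are OM-related". The rule taught is that acupuncture effects tend to be brief, while opioid effects last as long as the opioid is taken. Assessment of cause by two team members is described for serious events only.

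The Statistical analysis section names linear mixed models and generalised estimating equations for change over time in several outcomes, including numbers and types of opioid-related AEs. It then adds that chi-square "tests are also used to detect group differences in the numbers of dropouts and AEs". It does not say whether that test counts events or participants.

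**The concern.** A comparison of AEs defined by their cause is only as sound as the attribution of cause. Here participants are taught to make that attribution, and their ability to use the acupuncture label depends on their arm.

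- **No-EA:** no acupuncture is given during the 10 treatment weeks, so no symptom can be put down to it.
- **EA:** needling with de qi and strong stimulation gives a ready explanation for a symptom such as fatigue.
- **Sham EA:** needling is shallow, de qi is not intended and the stimulator does not work. The label is available, but there is less sensation to prompt it.

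Every report moved from the opioid to the acupuncture column lowers the opioid-related count in a needled arm. That is the direction hypothesis 3 predicts. It is also the direction of hypothesis 2 if EA participants relabel more than sham participants.

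A separate matter is the chi-square on AE numbers. A persistent symptom can be reported many times by one person. A test that treats those reports as independent understates the chance variation between arms.

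**Working it through.** **Inputs.** The article gives no AE rate, power or sample size for the AE hypotheses, so there is no planned figure on this point to reproduce. Arm sizes follow from 316 at 2:1:1: 316 x 2/4 = 158 EA, and 316/4 = 79 each for sham and no-EA. The 316 itself concerns opioid dose. It is reproduced closely: 1.5 x (2.576 + 0.842)^2 / 0.48^2 = 76.1, so 77 sham and 4 x 77 = 308 in total (312 with the t distribution, two-sided 1%). It is used here only for arm sizes. Fatigue rates, relabelled fractions and variance-to-mean ratios are assumptions, shown as ranges.

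**1. The two lists.**
- Opioid-related, common: somnolence, mental clouding, nausea, constipation.
- Opioid-related, uncommon: fatigue, itching, adverse mood changes, dry mouth.
- Acupuncture-related: dizziness, fatigue, pain, bruising, infection.

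The overlap is one symptom of the eight opioid-related ones, namely fatigue. No rule says on which scale, or in which column, a fatigue report belongs when the participant is unsure.

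**2. Relabelling, EA versus no-EA, no true effect.** Rate labelled opioid-related = true rate x (1 - fraction relabelled). With 30% relabelled in EA and 0% in no-EA, tested at a nominal 5% on participants with opioid-labelled fatigue (40,000 simulated trials):
- true 20%: 14% v 20%, rejected 23% of the time
- true 30%: 21% v 30%, rejected 34%
- true 50%: 35% v 50%, rejected 60%

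Hand check of the middle row. The pooled rate is (0.21 x 158 + 0.30 x 79)/237 = 0.24. The null standard error is sqrt(0.24 x 0.76 x (1/158 + 1/79)) = 0.0588, so the critical difference is 1.96 x 0.0588 = 0.115. The actual standard error is sqrt(0.21 x 0.79/158 + 0.30 x 0.70/79) = 0.0609. The chance of exceeding the limit is 1 - Phi((0.115 - 0.09)/0.0609), about 34%. At a nominal 1%, the level the article uses for the primary outcome, the simulated figure is 15%.

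**3. Relabelling, EA versus sham, no true effect.**
- Equal relabelling (30% in both arms): rejected 5% of the time, so no bias.
- Unequal relabelling (40% EA, 20% sham): for true rates of 20%, 30% and 50%, the labelled rates are 12% v 16%, 18% v 24% and 30% v 40%, rejected 15%, 21% and 34% of the time.

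**4. Chi-square on event counts, two groups.** If per-person counts have variance-to-mean ratio phi, the true error of a nominal 5% test is 2 x [1 - Phi(1.96/sqrt(phi))]:
- phi = 1: 5%
- phi = 1.5: 11%
- phi = 2: 1.96/1.414 = 1.386, giving 17%
- phi = 3: 26%
- phi = 4: 1.96/2 = 0.98, giving 33%
- phi = 5: 38%

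Simulation with 158 and 79 participants (20,000 runs) agrees at the values it covered: 11% at phi = 1.5, 16-17% at 2, 26% at 3 and 38% at 5.

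**5. What the planned models cover.** Mixed models and GEE allow for repeated reports by one person, which deals with step 4. They take the labelled events as given, so they do nothing about steps 2 and 3.

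**The case against.** The strongest reply is that the plan can be read without either fault.

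- **Outcome.** Item 2 names its symptoms in advance and rates severity, not cause. The sentence on teaching participants is in the safety section, and nothing says that a participant's label removes a 0-10 rating. This stands: the bias is conditional on labels deciding what counts. The text neither says so nor excludes it.
- **Overlap.** Item 2 is headed as common AEs, and none of those four is on the acupuncture list. Fatigue is one uncommon symptom. This stands as a limit on size, since a total over eight symptoms would dilute the shift. But the same item lists and scores fatigue, and hypothesis 2 and the analysis section refer to opioid-related AEs without restricting them to common ones.
- **Blinding.** EA and sham participants are blinded, and the article reports that they could not tell the procedures apart in earlier use. This stands, and is why hypothesis 2 is exposed only under unequal labelling. It does not help hypothesis 3.
- **Wording of hypothesis 3.** It says AEs without limiting them to opioid-related ones. If all AEs were counted, relabelling would not matter. The AE outcome defined for efficacy is opioid-related, though, so that is the likelier reading.
- **Chi-square.** The sentence pairs AEs with dropouts, which are counts of people, so participants may be meant. In that case step 4 does not apply.

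A reader might infer that hypothesis 2 rests on participants' labels and a chi-square test. It does not: mixed models and GEE are named first for opioid-related AEs, and the chi-square is an addition. A reader might also take the error as 22-47% for phi of 2-4. That comes from a three-group test on 2 degrees of freedom, exp(-5.991/(2 x phi)), whereas the hypotheses are two-group contrasts.

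**Conclusion.** The point holds in conditional form.

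**Attribution.** Participants sort non-serious AEs by cause, fatigue is on both lists on different scales, and the no-EA arm cannot use one of the two labels during treatment. If labels determine the opioid-related count, EA versus no-EA is biased towards EA by design. The false-positive rate on fatigue alone is 23-60% at a nominal 5%, assuming 30% relabelling and true fatigue rates of 20-50%. EA versus sham is affected only if labelling differs: 15-34% for 40% against 20% relabelled, and 5% if it is equal.

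**Clustering.** If the supplementary chi-square counts events, its two-group error is about 17-33% for phi of 2-4. If it counts participants, and labelling is equal, it stays at 5%.

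None of the assumed rates comes from the documents, so these figures show the scale of the exposure and do not predict a result. The outcomes are secondary and the primary comparison is not touched. The change is still worth making, because it removes both problems at almost no cost.

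**What to change.** 1. Define the AE outcome for hypotheses 2 and 3 as the eight symptoms listed under Secondary outcome measures, including fatigue. Rate them on the 0-10 scale in all three arms at the same weeks, and count them whatever cause the participant gives.
2. Analyse them with the mixed model or GEE already planned.
3. Report participants' attribution descriptively only. State that a fatigue report is always kept on the 0-10 scale, whether or not it is also scored as an acupuncture effect.
4. Run the chi-square on participants with at least one AE, not on numbers of events.

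This changes analysis wording and needs no new instrument, provided the 0-10 ratings are collected in every arm at the same weeks. The downside is small: some short-lived acupuncture symptoms will count against EA, which makes the comparison slightly conservative.

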### Data storage and access

All participants’ files are kept in a coded order in secure locked cabinets. Consent forms and personal information are stored separately from study questionnaires. Data in electronic files are de-identified and files are stored as password protected intranet files at the trial administration centre. Only authorized research personnel have access to hard and soft copies of the files. The information is retained for 15 years. After that information will be shredded and disposed of according to university procedure. Only aggregated data will be presented in publications.

### Statistical analysis of the trial outcomes

The Statistical Program for Social Science (SPSS, the latest version) is used for data analyses. Baseline categorical data, demographic characteristics such as gender and age category, and numerical data are analysed with *χ*^2^ tests and one-way analysis of variance, respectively, to determine comparability of the three groups on these variables.

Linear mixed models (for continuous outcome variables) and generalised estimating equations (for categorical outcome variables) are used to examine the changes over time in weekly dosage of OM, numbers and types of OM-related AEs, severity of pain and Beck Depression Inventory. *χ*^2^ tests are also used to detect group differences in the numbers of dropouts and AEs.

Both intention-to-treat and per protocol analyses are used. Data from participants who do not violate the treatment protocols will be included in the per protocol analysis. Missing data are dealt with using the last value carried forward method. Missing Beck Depression Inventory and SF-36 data are dealt with according to the relevant manual.

Apart from the effects of types of intervention, the influence on the outcomes of differences between centres and therapists is also analysed. The relationship between OM reduction and attitude to pain are explored.

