### Power and sample size calculation

Using sample means from baseline and the end of the treatment phase of the OM consumption data from our pilot study [19], we estimate that a total sample size of 316 will provide 80% power using a 1% level of significance to detect an effect size estimate of 0.48 between the EA and sham EA groups. Because intention-to-treat analysis will be used, no additional participants are required. We plan to recruit 316 participants in total. A dropout rate of 20% is considered to be within the normal range.

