### Randomisation and blinding procedures

After a four-week run-in period, participants who meet all selection criteria are randomly allocated into one of the three groups, namely EA, sham EA or no-EA with a 2:1:1 ratio. An automated telephone randomisation service provided by the National Health and Medical Research Council Clinical Trial Centre at the University of Sydney is used. Before the commencement of the first acupuncture session, the treating acupuncturist dials a toll-free number and enters the identification codes of the trial, the acupuncturist and the site, and the baseline OM weekly dose (morphine equivalent). The participant is then randomly allocated to one of the three groups according to a computer-generated randomisation sequence. The acupuncturist records the allocation in a secure and separate file. The computer-generated randomisation uses stratified permuted blocks to ensure that an equal ratio of participants in EA and sham EA groups in each centre is assigned to each acupuncturist; and to ensure that an equal number of participants consuming high or low dose of OM is assigned to each group. The cut-off OM dose for high or low consumption is 560 mg (morphine equivalents) per week, decided upon by pain specialists on the team based on our pilot study and other published studies reporting average OM consumption by patients with chronic pain [22,23]. Three quarters of the participants are in either the EA or sham EA group and are blinded; one quarter of the participants are in the no-EA group and are be blinded. The success of blinding of the two acupuncture groups is assessed. Details are presented in Assessment of efficacy below.

The acupuncturists and MDs are not involved in outcome assessments. Blinded assessors are required to conduct outcome assessments, collect Medication and Pain Diaries, and check any missing data. The trial data are entered by research assistants and analysed by a statistician. Except for the acupuncturists, all of the above will be are blinded to participant allocation. Professional statistical assistance is also sought to double check the data analysis.

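### The stated primary model does not name baseline opioid dose or the dose stratum as terms, and the scale of change is left open; naming them would gain precision at no cost

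*Protocol article*

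**What the plan says.** All references are to the protocol article.

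- **Outcome.** Under Primary outcome measure: "The primary outcome measure is the change in OM between baseline and the end of the treatment period". Doses are converted to morphine equivalents. Whether the change is absolute or relative to baseline is not said.
- **Design.** Randomisation and blinding procedures describes permuted blocks stratified by centre and acupuncturist and by baseline dose, the latter so that "an equal number of participants consuming high or low dose of OM is assigned to each group". The cut is 560 mg per week. Table 1 and Primary outcome measure show an opioid diary over weeks 1 to 4, before treatment.
- **Model.** Statistical analysis of the trial outcomes: "Linear mixed models (for continuous outcome variables) and generalised estimating equations (for categorical outcome variables) are used to examine the changes over time", with weekly opioid dosage first among the variables listed. No covariates and no transformation are named. A later sentence adds that "the influence on the outcomes of differences between centres and therapists is also analysed". The dose stratum is not mentioned in that section.
- **Baseline.** Chi-square tests and one-way analysis of variance are applied to baseline variables "to determine comparability of the three groups on these variables".

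**The concern.** Baseline dose is likely to be the strongest single predictor of week-14 dose. It is measured over four weeks and was important enough to be a stratification factor. Subtracting it, as a change score does, uses it less efficiently than regressing on it. Leaving stratification factors out of a linear model also makes the estimated standard error too large on average. Both losses fall on the EA versus sham contrast for which the trial is sized, and both can be avoided with data already collected.

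The scale is also loosely fixed. The modelled variable is a weekly dose, but the reduction schedule (Pain medication management), the pilot result of 39% against 25% (Electroacupuncture) and the responder outcome of 50% are all percentages. A change in mg and a change as a percentage of baseline weight participants very differently. A primary outcome that allows either leaves room to choose after the data are seen.

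The baseline significance tests cannot establish comparability, because after proper randomisation any difference is due to chance.

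**Working it through.** **1. Reproduce the plan's figure.** Power and sample size calculation states that "a total sample size of 316 will provide 80% power using a 1% level of significance"; the planning difference for EA versus sham is 0.48 SD. Allocation 2:1:1 of 316 gives 158 EA, 79 sham and 79 no-EA. The article does not say whether the test is one- or two-sided; two-sided is taken here because it reproduces the total.

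Sham n = (1 + 1/2) × (2.576 + 0.842)² / 0.48² = 1.5 × 11.68 / 0.2304 = 76.03, so 77, and the total is 4 × 77 = 308. The exact t calculation gives 78 and 312. A one-sided test gives 264.

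Power at 158 v 79: 0.48 / √(1/158 + 1/79) = 0.48 / 0.1378 = 3.484; Φ(3.484 − 2.576) = Φ(0.908) = 0.818 (0.811 by t). The stated 316 stands.

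**2. Direction of the gain.** Let baseline and end dose have SDs σb and σe and correlation ρ.

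- Change-score variance: σe² + σb² − 2ρσeσb
- Baseline-adjusted variance: σe²(1 − ρ²)
- Difference: (σb − ρσe)², which is never negative

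So adjustment does not lose to the change score whatever the SDs, apart from one degree of freedom. With equal SDs the ratio of adjusted to change-score variance is (1 − ρ²) / [2(1 − ρ)] = (1 + ρ)/2.

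**3. Size, if 0.48 is in SDs of the change.** Power = Φ(3.484 / √((1 + ρ)/2) − 2.576). The article gives no ρ, so a range is assumed.

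| ρ (assumed) | variance ratio | power, change score | power, adjusted | total N for 80%, adjusted |
|---|---|---|---|---|
| 0.5 | 0.75 | 0.818 | 0.926 | 232 |
| 0.7 | 0.85 | 0.818 | 0.885 | 260 |
| 0.9 | 0.95 | 0.818 | 0.841 | 292 |

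**4. Size, if 0.48 is in SDs of the end value.** The source is described as "Using sample means from baseline and the end of the treatment phase of the OM consumption data from our pilot study", with no SD given, so this reading is possible too. The change-score SD is then √(2(1 − ρ)) and the adjusted SD √(1 − ρ²). Change score against adjusted: 0.818 v 0.926 at ρ = 0.5, 0.973 v 0.989 at 0.7, both about 1.0 at 0.9. At a lower ρ of 0.3 it is 0.644 v 0.859.

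**5. Zero doses and the log scale.** The schedule asks for a 75% to 100% reduction by week 14, so zero doses are expected. An illustrative simulation (1,500 trials, 158 v 79, two-sided 1%) assumed lognormal baseline doses with median 560 mg and log-SD 0.8, mean log effects matching 39% and 25% reductions, and residual log-SD 0.4. Its power was:

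| analysis | no zeros | 10% at zero in both groups |
|---|---|---|
| mg, baseline-adjusted | 0.57 | 0.30 |
| percentage change | 0.85 | 0.57 |
| log(OM+5), baseline-adjusted | 0.87 | 0.06 |

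The levels depend on the assumed values. What carries over is that a log with a small added constant breaks down once a modest share of participants stop. log(OM+1) uses a smaller constant and puts zeros still further from the rest.

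**The case against.** The strongest reply is that a journal article need not list covariates, and a fuller protocol or analysis plan may do so. That stands, and it rules out several stronger readings.

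- A reader might infer that significance tests at baseline are used in place of adjustment. The article states the tests and the model separately. Nothing says one replaces the other or that adjustment is excluded.
- A reader might infer that the primary model ignores stratification altogether. Centre and therapist are to be analysed; the article does not say whether they are terms of the primary model. Only the dose stratum goes unnamed.
- A mixed model may hold the baseline weeks as outcomes. With a common baseline mean across groups it is about as efficient as baseline adjustment, and most of the gain is already in hand. With free group-by-time means it behaves as a change score. The text fits both.
- A reader might infer that untransformed mg was chosen and that this costs most of the power. The text names a weekly dosage but does not exclude a percentage. Nor can the loss be sized from the documents: an SD of 29 percentage points comes only from 14/0.48, where 14 is the pilot difference 39 − 25. Using it assumes that 0.48 lies on the percentage scale and so hands that scale about 80% power by construction. If 0.48 lies on the dose scale, the mg analysis has the planned power instead.

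What remains is that the article names an outcome, a model and the place of centre and therapist, and on that wording the efficient analysis is not secured.

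**Conclusion.** The point holds as one of precision and pre-specification. On a change-score or unconstrained reading, with 0.48 in change-score SDs, equal SDs at both times and ρ between 0.5 and 0.9 (all assumed), baseline adjustment adds about 11 points of power at ρ = 0.5 and about 2 at ρ = 0.9. It adds less if the model already constrains the baseline mean. The scale of the primary change is not fixed, and the choice between mg and percentage is a genuine trade-off, not an error in one direction. The baseline tests are poor practice, but dropping them alters no primary result. A reader might take this as evidence of bias or of an undersized trial. Neither follows: randomisation protects the unadjusted contrast, and the stated 316 reproduces.

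**What to change.** State the primary analysis as follows:

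- **Model.** A mixed model of post-baseline weekly opioid dose with treatment, week and their interaction; mean weekly dose over weeks 1 to 4 as a continuous covariate; and dose stratum, centre and acupuncturist as terms. The acupuncturist code entered at randomisation can serve for all three arms.
- **Test.** The EA versus sham contrast at week 14, at the 1% level used for sizing.
- **Scale.** Say whether the primary change is in mg or as a percentage of baseline, and give the other as a sensitivity analysis. State how zero doses are handled, and do not use log(OM+1).
- **Baseline table.** Descriptive, without significance tests.

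The cost is wording only. Every covariate is already collected, and the Trial status section says recruitment is open. The trade-off lies in the scale: mg gives high-dose users more weight, while a percentage is less stable for low starting doses and gives a relative headline result.
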